### Data collection

Data collection consists of a standard participant survey (including questions on food frequency, daily levels of occupational and recreational activity, smoking, hours of sleep, medical conditions and medication use), anthropometric data, blood tests, an inventory of activity, the completion of validated health, stress and diabetes quality of life surveys and cost. The costs will include cost associated with the program, monitoring and ongoing medical care. Initial data collection will occur prior to commencement of the CHIP intervention. Repeat data collection time points for both groups will be at the end of the 12-week intervention and again at 12 months from the initial commencement date.

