### Study setting

The CHIP intervention will be conducted by CHIP trained volunteers in selected community halls on the Central Coast of NSW. A demographic and lifestyle survey will be administered at the venue the intervention is conducted. Anthropometric measurements and blood collection will occur at the venue at which the CHIP intervention is being conducted unless the facility is not suited for medical data collection in which case it will be collected at selected general practices.

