### Allocation of participants to a study group

Invitees who are willing to participate will be recorded on a list until such time as there are between 30 and 40 individuals listed. At this point, the individual participants will be randomized into either Group 1 or Group 2.

Once allocated, participants in Group 1, will receive the CHIP intervention over a period of 12 weeks. At the end of the 12 weeks period, Group 1 will receive monthly follow-up for a further 9 month period. This process will be repeated, until the full number of participants have been collected and assigned.

An overview of the study design and allocation of participants is illustrated in Fig. 1.

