### Randomisation

The randomisation of participants will be performed by a person independent of the research team. The process of randomisation will occur with the aid of a computer. No blinding will be applied.

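### Baseline is tied to the start of CHIP and not to randomisation, so in this open trial the plan permits it to be collected after participants know their arm

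*Protocol article*

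**What the plan says.** The Data collection section gives one rule for the timing of baseline: "Initial data collection will occur prior to commencement of the CHIP intervention". The Statistical analysis section uses the same anchor, describing the first set of summaries as those at the start of the programme.

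Allocation of participants to a study group sets out the order of entry. "Invitees who are willing to participate will be recorded on a list until such time as there are between 30 and 40 individuals listed". Then: "At this point, the individual participants will be randomized into either Group 1 or Group 2". And next: "Once allocated, participants in Group 1, will receive the CHIP intervention over a period of 12 weeks". The Randomisation section adds: "No blinding will be applied".

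Study setting says where data are gathered. For the survey: "A demographic and lifestyle survey will be administered at the venue the intervention is conducted". Body measurements and bloods are also taken at the CHIP venue by default, with certain general practices as the fallback where a hall cannot be used for this. That section gives places and does not say when the first measurements happen.

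**The concern.** In an unblinded trial, baseline is protected from the influence of allocation only if it is complete before the arm is disclosed. Here the stated deadline is a later event, the start of the programme, and the only stated trigger for randomisation is the length of the list.

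Two things are at stake. First, people who know they are about to join a lifestyle programme may start changing diet or activity, or may answer questionnaires differently, before they are measured. The Limitations section already concedes that dietary, exercise and cost data depend on accurate self-report and that being measured may itself affect behaviour. Knowing one's arm could make those influences differ between arms. Laboratory values are less open to reporting bias, but can move if behaviour moves. Second, people allocated to usual care may lose interest and leave before giving any data, so that those with a baseline are no longer the full randomised group.

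**Working it through.** The point concerns the order of procedures. The document states no figure to reproduce, so the check sets the sections side by side.

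**Order in the readable text**

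1. Willing invitees are listed until there are 30 to 40 (Allocation).
2. The list is randomised. Its length is the only trigger named (Allocation).
3. Group 1 receives CHIP after allocation (Allocation).
4. Initial data collection must precede the start of CHIP (Data collection).

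Step 4 sets an upper limit on the time of baseline, and that limit is step 3. Nothing readable sets the limit at step 2. Baseline before step 2 complies, and so does baseline between steps 2 and 3. With no blinding, the arm can be known in that second window. Consent is required by the Ethical considerations section, but its place relative to baseline and randomisation is not given either.

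**Where a disturbed baseline would enter**

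Take an outcome for which lower is better. Let δ be the true between-arm difference at follow-up (negative if CHIP works), and suppose early behaviour change lowers the measured CHIP baseline by b > 0.

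- Paired pre-post test within the CHIP arm, which the Statistical analysis section names: the measured mean change is the true change + b, so the reduction looks smaller by b.
- Between-arm contrast of changes: δ + b.
- Between-arm contrast adjusted for baseline with slope β: δ + βb.
- Between-arm contrast of follow-up values only: δ. The shift in baseline does not enter.

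Early improvement in the CHIP arm therefore shrinks its measured benefit. If knowing the arm instead led CHIP participants to report a worse starting diet or activity level, b would change sign and the benefit would be inflated. The direction is not fixed.

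The loss of controls between allocation and baseline is a separate route. People who leave with no data are absent from every comparison, including the follow-up-only one.

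**Can a size be given?**

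It would need b, and the document gives nothing from which to estimate it. It would also need a scale. The Sample size estimate section states the target as a 3.5% reduction and the standard deviation as 20 without a unit, so the two cannot safely be put on one scale. Finally, it would need the contrast to use baseline. The independent t-test is described only as comparing data between groups, and the linear regression for survey scores names no baseline covariate. No magnitude is claimed.

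**The case against.** The strongest reply is that a baseline taken before randomisation fully satisfies the Data collection sentence, that nothing says baseline follows allocation, and that an article may leave the order of consent, measurement and randomisation to the full protocol. Fig. 1 is captioned as the overview of design and allocation and may show the order. Much of this stands: the text is permissive, the team may well intend baseline first, and the missing figure limits how firmly the point can be put. But the article does not leave the timing of baseline open. It names an anchor, uses it again in the analysis section, and the anchor is one that does not protect baseline in an open trial.

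Three stronger readings are tempting and are not supported.

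- A reader might infer that baseline will be taken after allocation. The text allows this but does not prescribe it.
- A reader might take collection at the CHIP hall as evidence of late timing. Study setting gives location, with general practices as a fallback, and a hall can host a session before a list is randomised.
- A reader might assume a one-arm shift of 1 to 2 units and divide by the target (1/3.5 = 29%, 2/3.5 = 57%) to claim a bias of that share. The shift is invented, the common unit is a guess, and the change-score contrast it applies to is not one the analysis section names.

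It is also fair to say that the early departure of controls is a possibility and not something the document reports.

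**Conclusion.** The point holds as a weakness in the stated timing rule. As far as the readable text goes, baseline may be collected after participants know their arm, because it is tied to the start of CHIP while open randomisation comes earlier and depends only on the list filling. The comparisons exposed are the paired pre-post tests and any contrast based on change or adjusted for baseline. Selective loss before baseline could reach the follow-up comparison as well. Self-reported diet, activity, quality of life and cost are the most vulnerable measures.

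The direction is not fixed and no reliable size can be given. The conclusion rests on the article text alone, with Fig. 1 unseen. It is a cheap improvement and not evidence that the trial's baseline is in fact compromised.

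**What to change.** Replace the timing sentence in Data collection with one tied to randomisation, for example:

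> The survey, anthropometry and blood tests that form the baseline will be completed for every person on a list before that list is randomised. Allocations will be released only after the last baseline on the list has been recorded.

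Add to Allocation of participants to a study group that a list is ready for randomisation when it has reached its size and its baselines are complete. If Fig. 1 shows a different order, bring it into line.

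The batch design makes this easy, since each list already waits to fill. With 150 participants in lists of 30 to 40, there are about four or five lists (150/40 = 3.75; 150/30 = 5), so about four or five baseline rounds have to be held before allocation. The costs are that earlier session, a somewhat longer gap between baseline and CHIP start, and a few people measured who are then not randomised. The article reports no enrolments and recruitment about to begin, so a change made at that stage would cover every participant. Once a list has been randomised without a baseline, analysis cannot recover one that is free of knowledge of the arm.

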### Sample size estimate

The total sample required for this study is 150, with an equal number of participants in each arm of the study. The sample size was calculated on the following assumptions: a reduction in 3.5% of fasting glucose in the intervention group, an equal allocation of participants to each group as well as a 10% drop out rate. A standard deviation of 20 was used. This study is sufficiently powered d > 80% to detect a 3.5% reduction in fasting glucose using significance of 0.05 (95% confidence interval).

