### Study design

A parallel randomized control study design will be used. A cohort of 150 patients will be randomized into either an intervention or control group. There will be 75 participants in each of the two groups. For the purpose of this study Group 1 will be the intervention group and Group 2 the control group.

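### The stated power of more than 80% for a 3.5% fall in fasting glucose cannot be reproduced from the printed inputs; it is about 17% to 19% if the effect and the SD are on the same scale

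*Protocol article*

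**What the plan says.** All the inputs are in the protocol article, mainly under Sample size estimate.

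- Size: "The total sample required for this study is 150, with an equal number of participants in each arm of the study". Study design confirms it: "There will be 75 participants in each of the two groups".
- Effect: "a reduction in 3.5% of fasting glucose in the intervention group". No baseline or control mean is given.
- Variability: "A standard deviation of 20 was used". There is no unit, and nothing says whether this is the SD of a single measurement or of a change.
- Allocation and attrition: "an equal allocation of participants to each group as well as a 10% drop out rate".
- Claim: "This study is sufficiently powered d > 80% to detect a 3.5% reduction in fasting glucose using significance of 0.05". The same sentence adds a 95% confidence interval in brackets, which implies a two-sided test; sidedness is not stated otherwise.

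Statistical analysis names an independent t-test for comparing the groups and a paired t-test for change from before to after the intervention. It describes no baseline adjustment for glucose.

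**The concern.** The planned effect is small beside the SD printed with it: 3.5 against 20 is under a fifth of a standard deviation. Effects of that size normally need several hundred patients per arm, so 75 per arm with 80% power looks wrong on sight.

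Fasting glucose is the only variable used to size the trial, and the first stated aim concerns it. The Discussion and Conclusion expect the results to inform treatment and funding decisions. A reader who trusts the stated power would give a non-significant result more weight against the programme than it can bear.

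**Working it through.** **Inputs.** N = 150, so n = 75 per arm. After 10% dropout, 150 × 0.90 = 135, or 67 to 68 per arm; 67 is used below. Difference 3.5, SD 20, α = 0.05 two-sided, two-sample t-test.

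**Attempt to reproduce the stated power, same scale.**

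d = 3.5 / 20 = 0.175. Noncentrality = d × √(n/2).

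- n = 67: 0.175 × √33.5 = 1.01, against a critical value of 1.98. Power 17.1%.
- n = 75: 0.175 × √37.5 = 1.07, against 1.98. Power 18.7%.

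The claim of more than 80% is not reproduced.

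**What would give 80%.**

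- Sample size at d = 0.175: the normal approximation 2 × (1.96 + 0.8416)² / 0.175² gives 513 per arm; the t-test gives 514 (1,028 evaluable in total).
- Detectable difference at SD 20: 9.75 units (d = 0.49) with 67 per arm; 9.21 units (d = 0.46) with 75.
- SD at which 3.5 units is detectable: about 7.2 with 67 per arm; about 7.6 with 75.

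**More favourable readings of the same figures.**

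| Reading | Power |
|---|---|
| One-sided two-sample test, 67 to 75 per arm | 26% to 28% |
| Paired test within one arm, 20 as SD of the change, 67 to 75 patients | 29% to 32% |
| All 150 as one paired group, two-sided | 57% |
| All 150 as one paired group, one-sided | 69% |

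**SD read as 20 mg/dL (assumption).** The difference is then 0.035 × baseline mean, and the mean is not given. Two-sided, unadjusted t-test:

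| Assumed mean (mg/dL) | Difference | d | Power, 67 per arm | Power, 75 per arm |
|---|---|---|---|---|
| 140 | 4.9 | 0.245 | 29% | 32% |
| 200 | 7.0 | 0.350 | 52% | 57% |
| 250 | 8.75 | 0.4375 | 71% | 76% |

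Power reaches 80% when 0.035 × mean equals the detectable difference: 9.75 / 0.035 ≈ 279 mg/dL with 67 per arm, and 9.21 / 0.035 ≈ 263 with 75. A one-sided test lowers this to about 233–247. If the SD were 20 mmol/L, power would be about 5% at means of 7 to 10 mmol/L.

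**Adding an analysis the article does not state (assumption).** With SD 20 for single values and correlation r between baseline and follow-up, the effective SD is 20√(1 − r²) for baseline adjustment and 20√(2(1 − r)) for change scores. At 67 per arm, two-sided:

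- Mean 200 mg/dL, r = 0.7, adjusted: SD 14.3, d = 0.49, power 80%.
- Mean 180 mg/dL, r = 0.8, adjusted: SD 12.0, d = 0.525, power 85%.
- Mean 180 mg/dL, r = 0.8, change score: SD 12.6, d = 0.50, power 82%.
- On the same-scale reading (d = 0.175 before adjustment), r would have to be about 0.93.

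**The case against.** The strongest reply is that the article does not fix a standardised difference. The effect is relative, the SD has no unit, and the full protocol may hold the unit, the source and the baseline mean. This stands in part. The 17% belongs to one reading and cannot be called the trial's power outright, and the absence of those details from a condensed article is not itself the error.

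A second reply is that 80% can be reached. With an SD of 20 mg/dL for single values, a mean of 180 to 200 mg/dL and a correlation of 0.7 to 0.8, an adjusted or change-score comparison gets there. A reader might infer from the low figures that no sensible reading reaches 80%; the documents do not support that, and they give no baseline glucose by which to call a mean plausible or not. But these readings need a unit, a mean, a correlation and an analysis that the article does not print. They show how the number might have arisen; they do not make it follow from what is stated.

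A third reply concerns consequences. A reader might infer that a null result is the most likely outcome if the planned effect is true. That holds on the same-scale reading but not on all: at 200 mg/dL unadjusted power is 52–57%, slightly better than even.

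Lastly, 17% applies the 10% dropout to the 150 patients, which the text implies without saying so. Without dropout it is 19%, and the conclusion is unchanged.

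**Conclusion.** The statement is wrong as written. No reading that uses only the printed figures and the planned tests gives 80% power for a 3.5% reduction. With effect and SD on one scale, the shortfall is more than 60 percentage points (17% to 19% against more than 80%), and the detectable difference is nearly three times the planned one (9.75 against 3.5).

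The exact size depends on the unit of the SD, and the mg/dL figures depend on an assumed mean. The finding that the power claim does not follow from its stated inputs depends on neither.

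On the same-scale reading, a non-significant result would be expected about four times in five even if the true effect is the planned one, so such a result should not be taken as evidence against the programme. The point does not show that the trial must be enlarged: a misprinted SD or effect remains possible.

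**What to change.** Correct the Sample size estimate paragraph:

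1. State the unit of the SD, whether it refers to a single measurement or to a change, and the baseline mean to which the 3.5% applies.
2. If the SD or the effect is a misprint, correct it and show the calculation.
3. If the inputs stand, remove the claim of sufficient power for 3.5%. Taking 3.5 and 20 on one scale, restate power as about 17% after dropout (19% without), and the difference detectable with 80% power as about 9.75 units (about 9.2 without dropout).

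The cost is the rewording of one paragraph and a less favourable figure. The article reports no enrolments yet, so the change can be made before recruitment. No extra patients are needed.

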### Statistical analysis

All data collected will be coded and entered into IBM® SPSS® version 22 for Windows® (SPSS Inc., 2013) before analysis.

#### Analysis for research question 1 and 2

Descriptive statistics will be used to analyze demographic data, anthropometric measurement data, blood results and activity levels on commencement of the program and also at the described re-evaluation intervals. Descriptive statistics will include frequencies, percentage distribution, means, and medians as well as standard deviation from the mean.

The Shapiro-Wilk test will be used to determine normal distribution to decide on whether to use parametric or non-parametric testing for correlations and variance analysis. A paired sample t-test (dependent t-test) will be used to compare pre intervention data with post intervention (12 weeks) and pre intervention data with post intervention (12 months) data. An independent t-test will be used to compare data between intervention and control groups. Pearson’s correlation will be used to explore relationships between continuous variables. The dietary inventory, health survey, and quality of life survey will be independently scored and the results between groups compared using linear regression. The level of significance is set at *p* < 0.05.

#### Analysis for research question 3

To determine the cost benefit of the intervention, a cost-benefit analysis will be undertaken. The cost benefit analysis will involve assessment of beneficial effects of the intervention. The analysis will include benefits and costs attributed to the project and indirect costs. Therefore, where B represents all the benefits and C represents all the costs, the project will be considered beneficial if B-C > 0. A cost benefit ratio will also be calculated. Costs included in the analysis will include opportunity costs. Costs from published literature and from government agencies will be used wherever possible, for example, the Medical Benefits Scheme and Pharmaceutical Benefits Scheme.

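### A Shapiro-Wilk test on the trial data may choose the analysis method, and the protocol leaves unclear whether the between-group fasting-glucose comparison is subject to it

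*Protocol article*

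**What the plan says.** All references are to the protocol article.

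- **Statistical analysis, research questions 1 and 2.** The rule reads "The Shapiro-Wilk test will be used to determine normal distribution to decide on whether to use parametric or non-parametric testing". The end of the same sentence sets its scope: the result is used "to decide on whether to use parametric or non-parametric testing for correlations and variance analysis". The sentences that follow carry no condition: "An independent t-test will be used to compare data between intervention and control groups", a paired t-test is given for change from baseline at each later visit, and "Pearson’s correlation will be used to explore relationships between continuous variables". Survey scores are compared by linear regression. No non-parametric test is named, and no ANOVA appears.
- **Sample size estimate.** "This study is sufficiently powered d > 80% to detect a 3.5% reduction in fasting glucose", and "A standard deviation of 20 was used". No test is named, but a reduction paired with a standard deviation is a mean-type effect.
- **Data collection.** Measurements are taken before the programme starts, at 12 weeks and at 12 months, in both groups.

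**The concern.** A rule that picks the method from the data also picks what is estimated. A t-test compares means. A rank-sum test asks which arm tends to have the lower value, and it estimates the same shift only if the two distributions have the same shape. A rank-sum p-value does not answer whether mean fasting glucose fell by the amount in the sample-size section.

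The rule would be applied afresh to each outcome and visit. Fasting glucose could be compared by means at 12 weeks and by ranks at 12 months, and the two results would not be on one footing.

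The text also does not settle its own scope. The gate covers correlations and analyses of variance, yet the one correlation method named is stated as fixed. The comparisons that might count as analyses of variance are t-tests, also stated as fixed.

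**Working it through.** **1. Is the between-group comparison gated? The wording side by side.**

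| Item | Covered by the gate's stated scope? | Worded with a condition? |
|---|---|---|
| Pearson's correlation | Yes, expressly (correlations) | No |
| Independent t-test, group 1 against group 2 | Only if it counts as an analysis of variance | No |
| Paired t-test, before against after | Only if it counts as an analysis of variance | No |
| ANOVA | Yes | Not in the plan |

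Pearson's correlation is inside the gate and still worded without condition, so unconditional wording does not put a test outside it. No ANOVA is planned, so the t-tests are the most evident object of the words on variance. The between-group comparison is therefore plausibly gated, but this cannot be proved from the text.

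**2. If it is gated, how often would the method switch?**

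The protocol gives no figure to reproduce here. Inputs:
- From the protocol: 75 per arm and 10% dropout, so 75 × 0.90 = 67.5; 67 is used.
- Assumed: raw values tested in each arm separately at 0.05, with a switch if either arm rejects; normal or log-normal values with a stated CV. The protocol gives no pre-test level, tested quantity, distribution, baseline mean or unit for the SD.

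If one arm rejects with probability p, at least one of two independent arms rejects with probability 1 − (1 − p)². One run of 3,000 simulated trials per row gave:

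| Assumed distribution | One arm, p | 1 − (1 − p)² | At least one arm, counted directly |
|---|---|---|---|
| Normal | 0.055 | 0.107 | 0.105 |
| Log-normal, CV 0.10 | 0.132 | 0.247 | 0.255 |
| Log-normal, CV 0.133 | 0.208 | 0.373 | 0.379 |
| Log-normal, CV 0.20 | 0.384 | 0.621 | 0.613 |
| Log-normal, CV 0.30 | 0.699 | 0.909 | 0.910 |
| Log-normal, CV 0.35 | 0.790 | 0.956 | 0.955 |

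CV 0.133 is an SD of 20 on an assumed mean of 150 (20/150). Separate runs gave 0.61 to 0.65 at CV 0.20 and about 0.96 at CV 0.35.

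**3. Would the two visits be analysed differently?**

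With an assumed correlation of 0.6 between visits on the log scale, the pre-test reached different decisions at the two visits in 34%, 43%, 42%, 31%, 17% and 8% of trials, at CV 0.10, 0.13, 0.20, 0.25, 0.30 and 0.35. Disagreement peaks at moderate skew, where the pre-test is least decisive.

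**4. Does the switch damage error rates?**

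The t-test was compared with the two-stage rule (rank-sum test if either arm rejects normality, otherwise t-test) on the same samples: 67 per arm, 4,000 trials per row. The alternative is a shift of SD × √(2/67) × (1.960 + 0.842), set for 80% t-test power. For SD 20 that is 20 × 0.1728 × 2.802 = 9.68.

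| Distribution | Type I error: t-test | Type I error: two-stage | Power: t-test | Power: two-stage |
|---|---|---|---|---|
| Normal | 0.058 | 0.059 | 0.78 | 0.78 |
| Log-normal, CV 0.133 | 0.050 | 0.052 | 0.78 | 0.78 |
| Log-normal, CV 0.30 | 0.052 | 0.054 | 0.80 | 0.84 |

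The simulation error of a rate near 0.05 is √(0.05 × 0.95/4000) = 0.0034, so these type I errors cannot be told apart. The t-test alone holds its level at this size under moderate skew, so the gate protects against little.

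**The case against.** **The text limits the rule, and the t-tests are stated as fixed.** This stands in part. It rules out saying that the between-group comparison is certainly gated. It does not show that it is exempt, because Pearson's correlation is worded in the same fixed way and is expressly inside the rule.

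**The frequency is assumed.** This stands. A reader might infer that the main comparison will often be a rank test for which the trial was not sized. The documents do not support that: the switch rate runs from about 10% to 96% across the assumed distributions, and the sample-size section names no test.

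**No loss of validity is shown.** This also stands. A reader might infer that the two-stage procedure loses its nominal error rate. In the simulations it does not, and power is equal or slightly higher. What remains is the change in what is estimated.

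**A condensed article may leave the fallback test to the analysis plan.** Granted, and its absence is not the complaint. The article does state a rule by which the data choose the method, and states it in a way that conflicts with the sentences after it. That is a fault in what is written.

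**The gate loses no baseline adjustment.** Correct: the planned independent t-test does not adjust either. Adjustment belongs to the better replacement and is not something the gate takes away.

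**Conclusion.** The point holds in limited form. The protocol contains a data-driven choice of method whose reach over the fasting-glucose comparison is unclear. If the comparison is covered, the effect measure can move from a mean difference to a rank-based contrast, and can do so differently by outcome and visit. With 67 per arm, the switch would occur in about 10% of trials under normality, 26% at CV 0.10, 61-65% at CV 0.20 and 96% at CV 0.35. These figures rest on assumed log-normal values, raw data tested by arm, and a pre-test level of 0.05. Testing changes or residuals, or pooling the arms, would give other rates.

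Type I error stays at about 0.05 to 0.06, so the cost is to interpretation and comparability. Severity is minor to moderate.

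The total of 150 also cannot be reproduced from its stated inputs. With 3.5 and SD 20 read on one scale, a two-sided comparison needs 2 × (20/3.5)² × (1.960 + 0.842)² ≈ 513 per arm. That is a separate fault; the normality test neither causes nor worsens it.

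**What to change.** In Statistical analysis, research questions 1 and 2:

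1. Delete the Shapiro-Wilk sentence.
2. For fasting glucose and every other continuous outcome, fix in advance a linear model for the value at each visit, with group and the baseline value as terms and robust (heteroscedasticity-consistent) standard errors. Report the adjusted group difference with its 95% confidence interval at 12 weeks and at 12 months.
3. Name one scale per outcome now and use it at both visits. For fasting glucose, a log scale gives a percentage difference and so matches the way the sample-size effect is expressed. Whichever scale is chosen should be written down before any outcome is compared by group.
4. Keep a rank-based comparison only as a named sensitivity analysis, reported whatever the data look like.

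The cost is a small rewrite of one section. The baseline values are already collected in both groups, so no extra visit, measurement or participant is needed.

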### Limitations

Several factors may influence the results obtained in this study. Firstly, compliance with the intervention is paramount to the success of lifestyle modification programmes, but it is also difficult to measure actual compliance reliably. Some data collection, namely dietary analysis, exercise compliance and medical costs will rely on patient integrity and accurate reporting which may not necessarily be reliable.

A potential confounder is that of the Hawthorne effect in that the participants’ behaviour may be affected by the fact that data is collected at baseline and again at future intervals.

The outcomes of this study have the potential to inform decisions about patient treatment and potentially provide incentive for the provision of funded lifestyle- based preventive and restorative programs for patients diagnosed with T2DM.

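### No between-arm test of fasting glucose or the other clinical outcomes adjusts for baseline, and the plan does not say whether the paired or the independent t-test answers research question 1

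*Protocol article*

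**What the plan says.** Research question 1 (Aims and research questions) is comparative: it asks what changes occur in fasting glucose and the other clinical measures under CHIP relative to a control group on routine care.

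The Statistical analysis section names two kinds of t-test for questions 1 and 2. The first is pre-post: "A paired sample t-test (dependent t-test) will be used to compare pre intervention data with post intervention (12 weeks", with the same comparison repeated at 12 months. The second is between groups: "An independent t-test will be used to compare data between intervention and control groups". Linear regression is planned only for the dietary, health and quality-of-life instruments, and no covariates are named for it.

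Baseline values will be available. Under Data collection, "Initial data collection will occur prior to commencement of the CHIP intervention", and both groups are measured again at 12 weeks and at 12 months. Under Limitations, the article names the Hawthorne effect as a potential confounder, because "the participants’ behaviour may be affected by the fact that data is collected at baseline and again at future intervals".

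**The concern.** Two things are fixed poorly.

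First, an independent t-test takes no covariate. Part of the variation in follow-up glucose is predictable from the participant's own baseline, and the planned test either leaves that variation in the error term (follow-up values) or removes it by plain subtraction, which is not the most efficient way (changes). The text does not say which of the two is meant.

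Second, a paired test compares a group with its own past. It takes in anything that moves both arms, such as a response to being measured or medication changes made by the general practitioner. Only the comparison of arms removes these. The paired tests are listed first, and nothing says that the between-arm test decides. A report could therefore offer a significant fall in CHIP beside a non-significant one in control as evidence for the programme, although that pattern does not test question 1.

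**Working it through.** **Inputs from the article (Sample size estimate).** "The total sample required for this study is 150, with an equal number of participants in each arm of the study", so 75 per arm. The effect is "a reduction in 3.5% of fasting glucose in the intervention group". "A standard deviation of 20 was used". Attrition enters "as well as a 10% drop out rate", so 75 × 0.9 = 67.5, taken as 67 evaluable per arm. Alpha is 0.05, read as two-sided.

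**Assumptions, not in the article.**
- The correlation ρ between baseline and follow-up is 0.5 to 0.7.
- The SD is the same at both visits and in both arms, and the SD of 20 is that of a single value.
- The 3.5% means 3.5 units on the scale of the SD, so d = 3.5/20 = 0.175. The article gives no unit and no baseline mean.

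**The plan's own figure.** n per arm = 2(1.960 + 0.842)² × 20²/3.5² = 513, or 513/0.9 = 570 after dropout. The stated 75 per arm does not reproduce on this reading; power with 75 is 18.7%. That is a separate problem and serves here only as background.

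**Precision.** With n per arm, the variance of the between-arm estimate is:
- t-test on follow-up values: 2σ²/n
- t-test on changes: (2σ²/n) × 2(1 − ρ)
- ANCOVA on baseline: (2σ²/n) × (1 − ρ²)

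ANCOVA therefore has 1 − ρ² times the variance of the first and (1 + ρ)/2 times the variance of the second. These ratios do not depend on d. Power uses the noncentral t distribution with 67 per arm and d divided by the square root of the variance factor:

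| ρ | ANCOVA vs follow-up values | ANCOVA vs changes | Power, follow-up values | Power, changes | Power, ANCOVA |
|---|---|---|---|---|---|
| 0.5 | 0.75 | 0.75 | 17.1% | 17.1% | 21.3% |
| 0.6 | 0.64 | 0.80 | 17.1% | 20.3% | 24.2% |
| 0.7 | 0.51 | 0.85 | 17.1% | 25.5% | 29.1% |

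In sample-size terms, the gain over follow-up values is 1/0.75 = 1.33 to 1/0.51 = 1.96 times. Over changes it is 1.33 times at ρ = 0.5 and 1/0.85 = 1.18 times at ρ = 0.7.

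**Sensitivity to the effect size.** If 3.5% is taken of an assumed baseline mean of 126 to 200 in the unit of the SD, the difference is 4.41 to 7.0 and d is 0.22 to 0.35. Unadjusted power is then about 24% to 52%.

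**Paired tests.** Suppose CHIP has no effect and both arms improve by the same amount δ, in units of the SD of change. Each arm's paired test has noncentrality δ√67 and power p. The arms are independent, so significance in CHIP but not in control has probability p(1 − p).

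| δ | p | p(1 − p) |
|---|---|---|
| 0.175 | 0.292 | 0.207 |
| 0.24 | 0.490 | 0.250 |
| 0.30 | 0.677 | 0.219 |

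The product peaks at 0.25 when p = 0.5. With no shared change it is 0.05 × 0.95 = 0.048, and it falls again once the shared change is large enough for both arms to be significant nearly always. A between-arm test holds 5% throughout.

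**The case against.** The planned between-arm test is sound: under randomisation an unadjusted t-test is unbiased and holds its error rate, and its standard error already covers chance imbalance at baseline. This stands.

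A reader might infer that the baseline is simply thrown away. The article does not support that. Question 1 speaks of changes, so the data compared may well be change scores, and baseline would then be subtracted. Against that reading the gain at ρ = 0.7 is 1.18 times the sample, not 1.96. ANCOVA still does better at every correlation considered.

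A reader might also infer that the trial intends to claim effectiveness from within-arm significance. No sentence says so, and a between-group test is planned. That the paired tests are run separately by arm is the natural reading but is not stated. The 21% to 25% measures what the pattern would be worth if it were used, under an assumed shared improvement. Nor does the article predict such an improvement: it says only that behaviour may be affected, and recruitment on a diabetes diagnosis, with no glucose threshold, documents no selection that would make regression to the mean certain.

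Leaving the matter to a statistical analysis plan does not answer the point, because the article has already named the tests.

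**Conclusion.** The point holds as one of efficiency and of an undefined deciding analysis, not of bias in the between-arm test. Research question 1 has no named deciding test, the quantity compared is left open, and a baseline value measured in both arms is adjusted for in none of the between-arm analyses of clinical outcomes.

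At an assumed ρ of 0.5 to 0.7, adjustment cuts the variance to 75% to 51% of that of a t-test on follow-up values, or to 75% to 85% of that of a t-test on changes. On the assumed d = 0.175, power with about 67 per arm rises from about 17% to 21–29%, or from 17–26% to 21–29% if changes were meant. It would be wrong to infer that adjustment repairs the sample size: on that reading 80% needs ρ of about 0.93. The paired tests cannot stand in for the randomised comparison. Under no CHIP effect and an equal improvement of 0.175 to 0.30 SD of change, they favour CHIP alone in about 21% to 25% of trials.

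**What to change.** For each continuous clinical outcome, at 12 weeks and at 12 months, make the analysis for question 1 a linear model of the follow-up value on arm and that outcome's own baseline value. Report the adjusted difference between arms with its 95% CI, and state that this contrast answers the question.

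A mixed model with both follow-up visits and baseline as covariate is an alternative. It also keeps participants with one missing visit, so it is not the same analysis; the plan should name one of the two. The text should also say how the Shapiro-Wilk step applies to the chosen model.

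Report pre-post changes descriptively, as means with CIs, and do not use paired p-values as evidence of a CHIP effect.

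The cost is a revision of the analysis wording. No new data are needed, and linear regression in SPSS is already planned for the surveys. The Study status section says recruitment was only about to begin, so at that stage the change could be made before any outcome was seen.
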